Furthermore, our clinical experience of GHB/GBL withdrawal in outpatient settings has been that patients who slowly reduce their GHB/GBL use describe significant anxiety and cravings during the few days before commencing medically assisted detoxification. For some, this acted as a deterrent to attending for treatment and a trigger for using higher doses of GHB/GBL. Consequently, we have initially used baclofen 2 days prior to stopping GHB/GBL in a small number of patients. There was very positive feedback from patients regarding the benefit, particularly in terms of reduced cravings and helping to stabilise pre-detoxification GHB use. The use of baclofen in our outpatient clinical service prior to initiating medically assisted detoxification has now become more widespread. The 2 days of pre-detoxification ‘preloading’ of baclofen at a standard dose of 10 mg three times a day has not resulted in any clinical incidents in relation to baclofen. This preloading with baclofen has previously not been formally studied to determine the usefulness of baclofen itself, neither has whether some of the reported benefits relate more to engagement with drug treatment services pre-detoxification than to baclofen itself.

Baclofen has been licensed in the UK for many years for the treatment of spasticity (maximum, 100 mg per day) and can be safely prescribed to a wide range of patients (see Summary of Product Characteristics (SPC), https://www.medicines.org.uk/emc/medicine/23850). Our clinical experience is that it is associated with few side effects. Whilst a withdrawal state is recognised for baclofen, this is unlikely to occur with its use in acute GHB withdrawal due to the short duration (7 to 10 days) of baclofen use in this indication. We suggest that the risk of complications from baclofen withdrawal is considerably less than that of inadequately managed GHB/GBL withdrawal [15, 18]. Nevertheless, whilst the use of baclofen holds promise, there are potential adverse effects on cardiovascular, neurological and respiratory systems so controlled data is urgently required to determine its efficacy and safety in GHB/GBL withdrawal. Optimising outpatient treatment to reduce the risk of complications and hospital admission is important since many individuals decline admission [17, 25]. Despite this complexity and its impact on, and cost to, the individual and the NHS, there is limited knowledge about how to best treat people in planned or unplanned GHB/GBL withdrawal.

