### Assessment and outcome measures

Data will be collected to inform the primary and secondary outcome measures in the definitive trial (see Table 1). The proposed primary outcome measures include symptom severity, complications and requirement for treatment escalation, and the proposed secondary outcomes include change in anxiety, depression, sleep and quality of life as well as relapse to GHB/GBL use or change in other illicit drug or alcohol use 30 days after the start of detoxification.

**Table 1 Tab1:** Assessment schedule of quantitative measures

Assessment	Baseline or as soon as data can be obtained	Daily during detoxification			Last day of detoxification or next working day	Ad hoc	30 days post start of detoxification
		Inpatient	Weekday outpatient	Weekend outpatient			
CIWA-Ar	✓	✓	✓	✓	✓		
Sedation Assessment Tool	✓	✓	✓	✓			
Depression (PHQ-9)	✓				✓		
Anxiety (GAD-7)	✓				✓		
Sleep pattern questionnaire	✓	✓	✓	✓	✓		
Vital signs	✓						
Psychiatric history	✓						
Relevant past medical history	✓						
Concomitant prescribed medication	✓	✓	✓	✓	✓		
Lifetime GHB/GBL use questionnaire					✓		
Daily drug/alcohol/nicotine use questionnaire	✓	✓	✓	✓			
Time-life follow-back of alcohol and drug use					✓		
AUDIT (alcohol)					✓		
Treatment Outcome Profile					✓		
Client Satisfaction Questionnaire (CSQ-8)					✓		
Adverse events		✓	✓	✓		✓	
Expected events associated with GHB/GBL withdrawal						✓	
Protocol deviations						✓	
Follow-up GHB/GBL use questionnaire							✓
Follow-up drug/alcohol use questionnaire							✓
Follow-up service use questionnaire							✓

*AUDIT* Alcohol Use Disorders Identification Test, *CIWA-Ar* Clinical Institute Withdrawal Assessment for Alcohol, *GAD-7* Generalised Anxiety Disorder-7, *GBL* gamma-butyrolactone, *GHB* gamma-hydroxybutyrate, *PHQ-9* Patient Health Questionnaire-9

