Any complications arising during preload or detoxification will be recorded. These will be classified as adverse events if they are not one of the following predetermined events which are known to occur in acute GHB/GBL withdrawal or detoxification: agitation or aggression, hallucinations (visual, auditory and/or tactile), tachycardia, seizures, ataxia, sedation, tremor and/or sweating. All adverse events occurring from the time a participant signs the Consent Form until completion of the last study-related procedure will be recorded in the Case Report Form. Any serious adverse event which occurs in a participant will be reported immediately to the chief investigator (CI) and sponsor and, if stated orally, will be followed by a detailed written report.

On day 30 after the start of detoxification (benzodiazepine detoxification, not preload), the researcher will contact the research participant to obtain information about any subsequent use of GHB/GBL, other recreational drugs/novel psychoactive substances/alcohol as well as any medication (prescribed or otherwise obtained) taken and psychosocial treatment/support received for their GHB/GBL dependence. In addition, any issues or events that could be related to their detoxification will be recorded.

Patients will be asked to return any remaining study medication to the clinic so that a pill count can be performed to assess compliance.

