### Data analysis

The primary focus of this study is to assess the feasibility of undertaking a definitive trial. In particular, we will characterise the optimal recruitment rate and strategies and characteristics of the proposed primary outcome measures (symptom severity, complications, and requirement for treatment escalation). The main analyses will be descriptive and provide estimates of variability and effect size with 95 % confidence intervals. This will include the rate of recruitment, the proportion of people approached who consent to randomisation, the proportion who complete detoxification and the proportion who will complete the follow-up assessment. We will also describe the distribution of scores on the primary outcomes and estimate the variance of the measure in this population. Data for our proposed secondary outcomes in the definitive trial will include change in anxiety, depression, sleep and quality of life as well as relapse to GHB/GBL use or change in other illicit drug or alcohol use 30 days after the start of detoxification. We will also identify appropriate criteria, e.g. benzodiazepine requirement or withdrawal score for minimisation or stratification in the full RCT.

We will use ANCOVA adjusting for patients’ characteristics and relevant clinical data. Where there is follow-up, methods applied to longitudinal data will be appropriate since they are able to detect significant differences between arms but they can also detect changes of the outcome measure(s) over time. We will also conduct an interim analysis to characterise the number of adverse events in each arm as described above.

An interim analysis to characterise the number of adverse events in each arm will also be conducted. Treatment escalation (i.e. admission to ICU for those presenting to the ED (unplanned) and admission to the general hospital for those in the Club Drug Clinic (planned)) will be closely monitored. From our clinical experience of complications from GHB/GBL withdrawal, if five individuals in any one group require treatment escalation, the sponsor and IDMEC will be immediately informed and recruitment suspended until there has been a discussion and consideration of the protocol and trial continuing. Stopping rules will also be agreed which specify the point at which interim results will be judged to be sufficiently conclusive for it to be appropriate for the IDMEC to recommend that they consider early termination of the trial.

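### The interim adverse-event count by arm, as written, leaves out seizures, sedation, ataxia and tachycardia whatever their cause, severity or phase, although these events are recorded separately

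*Protocol article*

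**What the plan says.** **Definition.** Under Assessment and outcome measures, the protocol article states: "Any complications arising during preload or detoxification will be recorded". It then says that complications are "classified as adverse events if they are not one of the following predetermined events which are known to occur in acute GHB/GBL withdrawal". The listed events are "agitation or aggression, hallucinations (visual, auditory and/or tactile), tachycardia, seizures, ataxia, sedation, tremor and/or sweating". Nothing there limits the exemption by severity, seriousness, suspected cause or phase.

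**Use of the term.** The Data analysis section says: "An interim analysis to characterise the number of adverse events in each arm will also be conducted". It says much the same in the paragraph before, where it refers back to an earlier description.

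**Why safety data are wanted.** The Background section on GHB/GBL withdrawal and the GABA-B system says of baclofen that "there are potential adverse effects on cardiovascular, neurological and respiratory systems so controlled data is urgently required to determine its efficacy and safety".

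**Collection.** Table 1 has a separate row, "Expected events associated with GHB/GBL withdrawal", ticked only in the ad hoc column. The adverse events row is ticked in all three daily detoxification columns and in the ad hoc column. Table 1 has no preload column.

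**Other monitoring.** Under Data analysis, five treatment escalations in any one group are notified at once to the sponsor and the IDMEC, and recruitment is suspended. Escalation means ICU admission for unplanned participants and general hospital admission for planned ones.

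**The concern.** The list exists because these events are expected in withdrawal. In a randomised comparison that is no reason to leave them out of a by-arm count. Both arms undergo withdrawal, so the contrast between arms is what separates background events from any drug effect. Removing an event type before the arms are compared removes that information for exactly the events where individual attribution is hardest.

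Preload shows this most clearly. The objectives describe baclofen starting two days before GHB/GBL is stopped. Sedation or ataxia in those two days cannot simply be presumed to be withdrawal, yet the exemption applies there too.

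At stake is whether an excess of these events on baclofen would be visible in the one by-arm safety analysis that the article describes for use during the trial.

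**Working it through.** The plan states no figure on this point, so the main check sets its provisions side by side.

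**1. Count the exempt events.** Agitation or aggression, hallucinations, tachycardia, seizures, ataxia, sedation, tremor, sweating: 8 types.

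**2. Compare with the organ systems named for baclofen.** Tachycardia is cardiovascular. Seizures, ataxia and sedation are neurological. So at least 4 of the 8 lie in two of the three named systems. No respiratory event is on the list, so respiratory events stay in the adverse-event count. For seizures there is one further link: epilepsy that is not well controlled is an exclusion, on the balance of risk and benefit of prescribing baclofen.

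**3. Trace the definition into the interim analysis.** The interim quantity is the number of adverse events per arm. The only rule in the article for what counts as an adverse event is the one above. A listed event therefore contributes zero, in either arm.

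**4. Illustrate the effect.** Group sizes assume equal allocation: 60/3 = 20 per planned group and 28/2 = 14 per unplanned group. The article gives no event rates, so those below are assumptions. They are for one listed event, such as sedation.

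| Group size | Assumed rate, placebo v baclofen | Expected participants affected | Contribution to adverse-event count |
|---|---|---|---|
| 20 | 10% v 30% | 2 v 6 | 0 v 0 |
| 20 | 10% v 40% | 2 v 8 | 0 v 0 |
| 20 | 20% v 40% | 4 v 8 | 0 v 0 |
| 14 | 10% v 40% | 1.4 v 5.6 | 0 v 0 |

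The last column follows from the definition and holds for any rates.

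**5. Test the escalation trigger as a backstop.** For a group of n with escalation probability p, P(at least 5) = 1 − Σ(k = 0 to 4) C(n,k) p^k (1−p)^(n−k).

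| n | p | P(at least 5) |
|---|---|---|
| 20 (planned) | 4% | 0.001 |
| 20 | 10% | 0.043 |
| 20 | 20% | 0.370 |
| 20 | 25% | 0.585 |
| 14 (unplanned) | 20% | 0.130 |
| 14 | 30% | 0.416 |
| 14 | 50% | 0.910 |

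The 4% and 50% rows use the Background figures for patients needing acute medical care on benzodiazepines alone: 4% initially in the outpatient clinic and up to 50% in the ED. Treating these as escalation rates is an assumption. In a planned group the trigger is more likely than not to fire only once escalation is near 25%. It does not register listed events that lead to no admission.

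**The case against.** The strongest reply is that the events are recorded and monitored in other ways, and much of it stands.

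- **Recording and final reporting.** All complications are recorded, preload included, and the predetermined events have their own row in Table 1. Complications are a proposed primary outcome, and the main analyses promise effect sizes with 95% confidence intervals. A reader might infer that these events vanish from final reporting. The article does not support that.
- **Named harms.** A reader might infer that the protocol itself names these four events as feared effects of baclofen. It names organ systems only. Assigning the events to those systems is this review's step.
- **Daily measurement.** The SAT is daily in detoxification, and the text has pulse and other vital signs taken with each CIWA-Ar, which is also daily. So collection is not purely passive. Two limits remain: Table 1 ticks vital signs at baseline only, and none of these daily assessments is scheduled in preload.
- **IDMEC.** It would be too strong to say that no excess could reach the IDMEC. Escalations do, and nothing confines the committee to the adverse-event count. The reference back to an earlier description also leaves the content of the interim analysis somewhat open, and the full protocol may settle it.
- **Serious events.** It is tempting to conclude that a serious seizure escapes immediate reporting. That is a literal reading of text that is silent on serious predetermined events. It calls for a clarifying sentence and does not show a bypass.
- **Delirium.** Delirium is not on the exempt list, and the Abstract and the objectives already name it as a complication. It need not be listed again, and counting it as an adverse event as well is no defect.

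None of this alters the stated rule: the interim count by arm, as defined, excludes the eight event types.

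**Conclusion.** The concern holds in a limited form. Two provisions of the article, read together, leave eight event types out of the interim by-arm adverse-event count. At least four of them lie in organ systems for which the Background says controlled safety data are needed. Whatever the true difference between arms in these events, the count shows 0 v 0 from them. The gap lies in the interim count, the reporting status of serious listed events and the collection schedule. It is not a loss of data.

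The escalation rule only partly covers the gap: it is weak in the planned groups at escalation rates up to about 20%, and blind to events without admission. Those probabilities assume equal allocation and independent participants. The conclusion about the count depends on neither, only on reading the adverse-event definition as the one used at the interim, the sole definition the article gives.

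**What to change.** 1. In Data analysis, state that the predetermined events are tabulated by arm beside adverse events in the interim and final safety tables, regardless of presumed cause. Giving them their own lines, with preload shown apart from detoxification, leaves the adverse-event count itself unchanged.
2. In Assessment and outcome measures, limit the exemption to non-serious events, and state that a serious predetermined event follows serious adverse event reporting.
3. In Table 1, tick the expected-events row in the same daily columns as adverse events, and provide for its collection during preload.

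The cost is a few sentences, one row and preload coverage in Table 1, one extra interim table and longer listings. During detoxification the daily question can be asked with the adverse-event check already scheduled; preload needs a collection point of its own. Sample size, randomisation and the proposed outcomes are unaffected.

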### Study medication discontinuation and withdrawal from the study

In accordance with the current revision of the Declaration of Helsinki (amended October 2000, with additional footnotes added in 2002 and 2004), a participant has the right to stop trial treatment and to withdraw from the trial at any time and for any reason, without prejudice to his or her future medical care by the physician or at the institution, and is not obliged to give his or her reasons for doing so. The principal investigator’s clinical judgement will determine whether or not an adverse event is of sufficient severity to require discontinuation of the study treatment. A participant who discontinues the study medication before the end of their detoxification will not be withdrawn from the study. Provided they have not withdrawn their consent, they would continue to be followed up to enable an intention-to-treat analysis. In addition, as this is a feasibility study, they may be approached for the qualitative study.

### Study unblinding

Masking of treatment allocation will be maintained during an individual’s participation in the trial unless any of the following occur: a serious adverse event arises that clinically requires disclosure or another clinical reason to need to know the allocation such as to start the participant on medication which has a risk of interaction. The 24-h emergency unblinding service will allow a medical request for unblinding in the event of a medical emergency. Procedures will be put in place to verify the identity of the participant and caller, and the decision on whether to reveal the study medication allocation will be based on a set of criteria for judging clinical need. All requests for unblinding will be recorded.

### Sample size

The aim is to recruit 88 research participants who are undergoing GHB/GBL detoxification: 60 planned outpatients and 28 unplanned inpatients.

### Qualitative process evaluation: research participant and clinician acceptability

We will undertake qualitative, semistructured, one-to-one interviews with 12 research participants, 6 from each site. Informed consent will be separately sought for this aspect of the study. Participants will be sampled purposively to represent key case-mix variables and treatment allocation. These interviews will investigate (1) participants’ experience and acceptance of the study procedures (notably recruitment, randomisation and outcome assessment procedures) and (2) their treatment experience. The interviews will be conducted using a topic guide. This will be drafted on the basis of the study aims, relevant scientific literature and clinical experience, but there will be scope for iterative development of the guide as data collection and analysis progress. Participants who have undergone a previous detoxification will be asked to reflect on how the trial detoxification compared with previous ones.

In addition, two focus groups involving the clinical teams from each site will also be conducted. These will explore clinician experience of the trial and the acceptability of trial procedures. Key senior members of staff will also be offered a one-to-one semistructured interview. All interviews and focus groups will be audio-recorded, transcribed and analysed using a thematic framework approach and managed using NVivo (Scolari/Sage) computer software. Initial coding frameworks for both participant and staff datasets will be based on the study aims of how feasible and acceptable it is to undertake a definitive trial, but subthemes will be further developed through analytic induction and grounded in the data. This will be revised iteratively as data collection and analysis progress.

### Cost-effectiveness

Data will be collected to inform the undertaking of a full economic evaluation in the definitive randomised controlled trial (RCT) by piloting the data collection methods that would be used in such a full trial. Piloting data collection instruments will show the feasibility of recording service use information from the population and identify the services and other costs to participants that would need to be included in a full economic evaluation of a phase III trial.

### Safety monitoring plan

An Independent Data Monitoring and Ethics Committee (IDMEC) will be established to provide overall supervision of the trial and ensure that it is being conducted in accordance with the principles of Good Clinical Practice (GCP) and the relevant regulations. It will report to the Trial Steering Committee which provides overall supervision for the GHB trial on behalf of the trial sponsor and the trial funder, ensures that the trial is appropriately conducted, and provides advice, through its chair, to the Trial Management Group.

The end of the trial is defined as completion of follow-up of, or three attempts to contact, the last participant randomised to the study medication. The trial may terminate before all (*n* = 88) participants have been recruited if we have obtained sufficient information about recruitment, engagement and/or evaluation of outcome measures.

The NHS Indemnity Scheme applies and provides unlimited cover for NHS staff, medical academic staff with honorary contracts and those conducting research, for negligent harm. Non-negligent harm (i.e. harm that has been caused through no fault of those conducting research) is not covered by this scheme; however, ex gratia payments may be considered by the trust in limited circumstances.

### Trial monitoring

Each site in the trial will receive two on-site monitor visits, firstly when five participants have been randomised to the trial and a second site visit 6–9 months from the time of site activation. Additional monitor visits will be conducted if required. These will be conducted by the sponsor, CI and trial manager.

### Data

The anonymised data will be stored on a laptop and backed up on a secure server. The personal datasheet and code associated with that person will be kept locked up. All data handling and record keeping will adhere to the Data Protection Act 1998. Regarding access to source data, the sponsor and investigators will permit monitoring, audits, Research Ethics Committee (REC) and Medicine and Healthcare products Regulatory Agency (MHRA) review (as applicable) and provide direct access to source data and documents as appropriate.

### Data analysis

The primary focus of this study is to assess the feasibility of undertaking a definitive trial. In particular, we will characterise the optimal recruitment rate and strategies and characteristics of the proposed primary outcome measures (symptom severity, complications, and requirement for treatment escalation). The main analyses will be descriptive and provide estimates of variability and effect size with 95 % confidence intervals. This will include the rate of recruitment, the proportion of people approached who consent to randomisation, the proportion who complete detoxification and the proportion who will complete the follow-up assessment. We will also describe the distribution of scores on the primary outcomes and estimate the variance of the measure in this population. Data for our proposed secondary outcomes in the definitive trial will include change in anxiety, depression, sleep and quality of life as well as relapse to GHB/GBL use or change in other illicit drug or alcohol use 30 days after the start of detoxification. We will also identify appropriate criteria, e.g. benzodiazepine requirement or withdrawal score for minimisation or stratification in the full RCT.

We will use ANCOVA adjusting for patients’ characteristics and relevant clinical data. Where there is follow-up, methods applied to longitudinal data will be appropriate since they are able to detect significant differences between arms but they can also detect changes of the outcome measure(s) over time. We will also conduct an interim analysis to characterise the number of adverse events in each arm as described above.

An interim analysis to characterise the number of adverse events in each arm will also be conducted. Treatment escalation (i.e. admission to ICU for those presenting to the ED (unplanned) and admission to the general hospital for those in the Club Drug Clinic (planned)) will be closely monitored. From our clinical experience of complications from GHB/GBL withdrawal, if five individuals in any one group require treatment escalation, the sponsor and IDMEC will be immediately informed and recruitment suspended until there has been a discussion and consideration of the protocol and trial continuing. Stopping rules will also be agreed which specify the point at which interim results will be judged to be sufficiently conclusive for it to be appropriate for the IDMEC to recommend that they consider early termination of the trial.

